# Safety of tubal ligation by minilaparotomy provided by clinical officers versus assistant medical officers: study protocol for a noninferiority randomized controlled trial in Tanzanian women

**DOI:** 10.1186/s13063-017-2235-6

**Published:** 2017-10-26

**Keywords:** Task shifting, Tubal ligation, Minilaparotomy, Noninferiority randomized controlled trial

## Abstract

**Background:**

Female sterilization by tubal ligation is a safe, extremely effective, and permanent way to limit childbearing. It is the most popular modern contraceptive method worldwide. The simplest way to provide tubal ligation is by a procedure called *minilaparotomy*, generally performed with the client under local anesthesia with systemic sedation and analgesia. In Tanzania, unmet need for family planning is high and has declined little in the past decade. Access to tubal ligation is limited throughout the country, in large part because of a lack of trained providers. Clinical officers (COs) are midlevel health workers who provide diagnosis, treatment, and minor surgeries. They are more prevalent than physicians in poorer and rural communities. Task shifting—the delegation of some tasks to less-specialized health workers, including task shifting of surgical procedures to midlevel cadres—has improved access to lifesaving interventions in resource-limited settings. It is a cost-effective way to address shortages of physicians, increasing access to services. The primary objective of this trial is to establish whether the safety of tubal ligation by minilaparotomy provided by COs is noninferior to the safety of tubal ligation by minilaparotomy provided by physicians (assistant medical officers [AMOs]), as measured by rates of major adverse events (AEs) during the procedure and through 42 days of follow-up.

**Methods/design:**

In this facility-based, multicenter, noninferiority randomized controlled trial, we are comparing the safety of tubal ligation by minilaparotomy performed by trained COs versus by trained AMOs. The primary outcome is safety, defined by the overall rate of major AEs occurring during the minilaparotomy procedure and through 42 days of follow-up. The trial will be conducted among 1970 women 18 years of age or older presenting for tubal ligation at 7 study sites in northern Tanzania.

**Discussion:**

If no major safety issues are identified, the data from this trial may facilitate changes in the Tanzanian government’s regulations, allowing appropriately trained COs to provide tubal ligation by minilaparotomy. Positive findings may have broader implications. Task shifting to provide long-acting contraceptives, if proven safe, may be an effective approach to increasing contraceptive access in low- and middle-income countries.

**Trial registration:**

ClinicalTrials.gov, NCT02944149. Registered on 14 October 2016.

**Electronic supplementary material:**

The online version of this article (doi:10.1186/s13063-017-2235-6) contains supplementary material, which is available to authorized users.

## Background

Female sterilization by tubal ligation is a safe, extremely effective, and permanent way to limit childbearing, and it is the single most popular modern contraceptive method worldwide [1]. The simplest way to provide tubal ligation is through a procedure called *minilaparotomy*, which is generally performed with the client under local anesthesia with systemic sedation and analgesia. According to the World Health Organization (WHO), tubal ligation by minilaparotomy is a minor surgery that can be performed in resource-limited settings on an outpatient basis with low risk of complications [2, 3]. Although data are limited and published reports are for the most part several decades old, complication rates of 0.7–3.4% following tubal ligation by minilaparotomy performed by physicians have been reported in several countries in Africa [4–9].

Among currently married Tanzanian women 15–49 years old, 25.7% do not want to have any more children, whereas 3.4% have had a tubal ligation [10]. Although modern contraceptive use has steadily increased over the last decade, from 20% in 2004–2005 to 27% in 2010 and 32% in 2015–2016, unmet need for family planning has remained steady at 22–24% since 1999 [10]. Use of tubal ligation among currently married women has more than doubled, from 1.6% in the early 1990s to 3.4% today; however, it represents only about 11% of all contraceptive use, despite the large numbers of women who desire no more children [10].

Despite a high demand for modern contraceptives, access to tubal ligation in Tanzania is limited, with 58% of hospitals and 38% of health centers offering tubal ligation services. (In some cases, only counseling is provided.) Availability is roughly evenly divided between government, private for-profit, and faith-based facilities [11]. The government of Tanzania (GOT) recognizes that most health facilities in the country are understaffed, with the greatest need in rural areas, and that a lack of trained providers significantly limits the availability of services, including tubal ligation [12]. Clinical officers (COs) are midlevel providers who diagnose and treat illnesses and perform minor surgeries. They outnumber physicians, both medical officers (MOs) and assistant medical officers (AMOs), by a 2:1 ratio, and they are more prevalent in rural communities [11].

Task shifting, described as delegation or shifting of some tasks to less-specialized health workers, is one method used to expand the health workforce [13, 14]. Task shifting of surgical procedures to midlevel cadres, including COs, has improved access to lifesaving interventions in resource-limited settings and is considered a safe and cost-effective way to address physician shortages [15]. Two recent systematic reviews of older studies, as well as two recent small-scale studies in Uganda and Malawi, suggest that task-shifting tubal ligation via minilaparotomy to nonphysician clinicians is safe, although available evidence is limited and well-designed clinical trials are needed to definitively demonstrate safety, efficacy, and acceptability of task-shifting the procedure to midlevel providers [16–19]. WHO guidelines on optimizing health workers’ roles for maternal and newborn health include COs among those considered competent to provide tubal ligation; however, the recommendation was not based on a review of evidence [20].

Task shifting of tubal ligation by minilaparotomy to COs would increase access to tubal ligation for many Tanzanian women who are most in need and is of interest to the GOT as a way to assist in meeting the needs of the growing numbers of women seeking permanent contraception. With this in mind, the primary objective of the present study is to establish whether the safety of tubal ligation by minilaparotomy, as measured by rates of major adverse events (AEs) during study participation, when provided by trained COs is noninferior to the safety of the procedure when provided by trained AMOs.

## Methods/design

This study is a noninferiority randomized controlled trial (RCT) comparing the safety of tubal ligation by minilaparotomy conducted by trained COs and by trained AMOs in Tanzania. We will randomize a total of 1970 women 18 years of age and older presenting at 7 sites for tubal ligation in a 1:1 ratio to have the procedure done by a CO or an AMO. In addition to the screening and enrollment/tubal ligation visit, there will be three scheduled follow-up visits at 3, 7, and 42 days postsurgery. Figure 1 depicts the flow of study participants. We have included a Standard Protocol Items: Recommendations for Interventional Trials (SPIRIT) checklist in Additional file 1.

**Fig. 1 Fig1:**
[figure not shown]
Trial profile

### Intervention

The study intervention is tubal ligation via minilaparotomy conducted by a CO in the intervention arm and by an AMO is the control arm. To ensure adequate skills to perform minilaparotomy, COs and AMOs (none of whom had prior experience performing tubal ligation by minilaparotomy) participated in competency-based training according to GOT guidelines and standards prior to the start of the study [21].

### Outcome measures

The primary objective is to establish whether the safety of tubal ligation by minilaparotomy as provided by COs is noninferior to the safety of tubal ligation by minilaparotomy as provided by AMOs. The primary study outcome is safety, defined by the overall rate of major AEs observed during the procedure and through 42 days of follow-up. We will compare the rate of major AEs observed following procedures conducted by COs with that of procedures performed by AMOs. Major AEs include the following:Injuries to abdominal viscera, pelvic abscess, or severe peritonitis leading to unintended major surgerySevere intra- or immediate postoperative hemorrhage requiring blood transfusionFebrile morbidity (oral temperature > 38 °C on at least 2 postoperative days, excluding the first 24 h after surgery)Life-threatening event (including cardiopulmonary crisis or anaphylaxis)Readmission to the hospital any time after discharge after the procedure through the end of follow-up, owing to a complication related to the minilaparotomy procedureDeath or complication resulting in death occurring within 42 days of the surgery related to the minilaparotomy procedure

Secondary objectives and their outcomes include comparison of the following:The safety of tubal ligation by minilaparotomy provided by COs versus AMOs as measured by AE rates (major and minor) at different points in time (intraoperatively, immediately postoperatively, and at each follow-up visit)The performance (e.g., procedure times, difficulties performing the procedure, inability to complete the procedure, need for assistance to complete the procedure, and maximum reported pain experienced by the participant during the procedure) of COs versus AMOs for conducting tubal ligation by minilaparotomyParticipant satisfaction with the tubal ligation conducted by COs versus AMOsThe self-efficacy of COs versus AMOs in performing tubal ligation by minilaparotomy, defined by provider confidence, comfort, and perception of their ability to perform the procedure

Detailed definitions of the primary and secondary outcomes, including the domain (name of the outcome), specific measurement, metric, method of aggregation, and time point for measurement can be found in Table 1.

**Table 1 Tab1:** Definitions and statistical methods for analyzing primary and secondary outcomes

Outcome	Specific measurement	Metric	Method of aggregation	Time point for measurement	Method of analysis for difference between COs and AMOs
Primary outcome					
Major AEs	AEs graded according to predefined criteria (*see* Additional file 2, Adverse event listing).	Presence of major AEs	Five-level ordinal categorical measure of AE severity, grouped as major (IIIa–V) or minor (I and II)	During the tubal ligation procedure and through 42 days of follow-up	Chi-square test
Secondary outcomes					
Major and minor AEs at different time points during the study	AEs graded according to predefined criteria (*see* Additional file 2, Adverse event listing).	Presence of major or minor AEs	Five-level ordinal categorical measure of AE severity, grouped as major (IIIa–V) or minor (I and II).	▪ Intraoperatively ▪ Immediately postoperatively ▪ 3 days postoperatively ▪ 7 days postoperatively ▪ 42 days postoperatively	Chi-square test.
Performance: procedure time	Time to event in minutes	Difference between procedure end time and start time	Continuous measure reported as mean procedure time	Intraoperatively	Independent sample *t* test
Performance: difficulties performing procedures	Yes/no	Reported occurrence	Categorical measure of proportion of occurrence		Chi-square test
Performance: inability to complete procedure	Yes/no	Reported occurrence	Categorical measure of proportion of occurrence		Chi-square test
Performance: need for assistance to complete procedure	Yes/no	Reported occurrence	Categorical measure of proportion of occurrence		Chi-square test
Performance: maximum reported pain experienced by participant during procedure	Visual analogue scale (0 = no pain, 10 = worst possible pain)	Reported level of pain	Continuous measure reported as mean pain score		Independent sample *t* test
Participant satisfaction with tubal ligation	Rating scale	Reported level of satisfaction	Four-category ordinal value (very satisfied, somewhat satisfied, somewhat dissatisfied, or very dissatisfied)	Day 3 and day 42 follow-up visits	Ordinal logistic regression
Self-efficacy of providers in performing tubal ligation by minilaparotomy	Self-administered confidence scale	Reported level of confidence	Continuous measure with higher value indicating greater level of confidence	At completion of recruitment	Independent sample *t* test
	Self-administered comfort scale	Reported level of comfort	Continuous measure with higher value indicating greater level of comfort		Independent sample *t* test
	Self-administered self-efficacy questionnaire adapted from the General Self-Efficacy Scale	Reported level of self-efficacy	Continuous measure with higher value indicating greater level of self-efficacy		Independent sample *t* test

*AE* Adverse event

### Study sites

We will conduct the study at seven sites based at health care facilities in northern Tanzania (Table 2). In addition to provision of tubal ligation services at these seven static sites, we will use outreach approaches that are currently part of the GOT’s approach to increasing access to family planning. During outreach events, the trained COs and AMOs from the seven static study sites will travel to and perform procedures at other facilities where tubal ligation is not routinely available. All seven of the static study sites, as well as the outreach sites, are currently part of the GOT family planning program, with tubal ligation by minilaparotomy normally provided by physicians who are not among the providers included in the study.

**Table 2 Tab2:** Study sites

District	Static study site
Arusha City	Daraja 2 Health Centre
	Kaloleni Health Centre
	Levolosi Urban Health Centre
Karatu District	Karatu Designated District Hospital
Longido District	Longido Health Centre
Monduli District	Monduli District Hospital
	Mto wa Mbu Health Centre

### Study population and eligibility criteria

We will recruit a total of 1970 participants from among women presenting at static or outreach study sites for tubal ligation. Study staff will ask women if they are potentially interested in participating in the study after they have undergone the standard GOT family planning counseling, chosen tubal ligation as the contraceptive option of their choice, and signed the GOT informed consent documents for the tubal ligation procedure.

We will randomize women if they meet any of the following criteria:Are aged 18 years or olderRequested and consented (in accordance with GOT procedures) to tubal ligation and additionally freely consented to participate in the study and signed a study informed consent formAre of sound mind, are in good general health, and are deemed suitable to undergo tubal ligation by minilaparotomy in accordance with the GOT guidelines [21]Are able to understand study procedures and the requirements of study participationAgree to return to the study site for the full schedule of follow-up visitsAgree to provide the study staff with an address, phone number, name of a close relative, and/or other locator information while participating in the research study

We will exclude women if they meet any of the following criteria:Are pregnantAre between 8 and 42 days postpartum or postabortionHave a known allergy or sensitivity to lidocaine or other local anesthesiaTake a medication that would be a contraindication for elective surgery, such as an anticoagulant or steroidHave had previous abdominal or pelvic surgeryHave a local skin infection near the area where the incision will be madeHave severe anemia (regardless of type or etiology), a coagulation disorder, hypertension (properly taken measurements: systolic pressure ≥ 160 mmHg or diastolic pressure ≥ 100 mmHg), acute deep venous thrombosis/pulmonary embolism, or current ischemic heart diseaseHave unexplained vaginal bleeding; malignant gestational trophoblastic disease; cervical, endometrial, and/or ovarian cancer; pelvic inflammatory disease (current or within the last 3 months); or current purulent cervicitis, chlamydial infection, and/or gonorrheaHave current symptomatic gallbladder disease, active viral hepatitis, tuberculosis of pelvic organs, acute bronchitis or pneumonia, or systematic infection or gastroenteritisAre currently participating in another biomedical research study

### Generation of allocation sequence and random allocation

We used permuted blocks within the site for the randomization to ensure similarity of groups with regard to potential confounding factors. A researcher unaffiliated with the study generated by computer the random allocation sequence centrally at EngenderHealth headquarters in New York City. Randomization is in a 1:1 ratio (minilaparotomy conducted by a CO or minilaparotomy conducted by an AMO), stratified by study site, and restricted with randomly varying block sizes of four to eight within the strata. We will recruit participants at all study sites until the total sample size has been reached. A research assistant at each site will randomize participants after screening has been conducted, a woman’s eligibility for study participation has been confirmed, and just prior to start of the minilaparotomy procedure. We will achieve random allocation concealment by using a text message service (Sealed Envelope Ltd. [www.sealedenvelope.com], London, UK). Because of the nature of the services and low availability of clinical staff at study sites, it is not possible to mask participants, coinvestigators, those assessing outcomes, or other study staff to treatment allocation.

### Rationale for the noninferiority hypothesis and sample size calculation

The primary objective of this study is to determine whether the rate of major AEs following tubal ligation by minilaparotomy conducted by trained COs is not worse by more than a minimal relevant difference than the AE rate following tubal ligation by minilaparotomy conducted by trained AMOs. This question lends itself to a noninferiority design. The choice of the noninferiority margin (i.e., the smallest clinical difference that is acceptable between the two treatments) is based on a combination of clinical judgment and statistical reasoning. In the case of major AEs following tubal ligation by minilaparotomy, data from prior trials (*n* = 12) suggest an average AE rate of 3.85% (95% CI 3.15–4.54%). After removing the one trial that is an outlier, in terms of both sample size and AE rate, we calculated the average as 1.59% (95% CI 0.90–2.28%) (Table 3).

**Table 3 Tab3:** Reported adverse event rates following tubal ligation by minilaparotomy

Reference	AEs (*n*)	Sample (*n*)	AE rate		
Chowdhury and Chowdhury, 1975 [31]	7	600	1.2%		
Fongsri and McDaniel, 1979 [32]	4	900	0.4%		
Dusitsin et al., 1980 [33]	5	292	1.7%		
Koetsawang et al., 1981 [34]	37	1376	2.7%		
Satyapan et al., 1983 [35]	82	3549	2.3%		
Kanchanasinith et al., 1990 [36]	8	820	1.0%		
Jack and Chao, 1992 [8]	482	5182	9.3%		
Ruminjo and Ngugi, 1992 [6]	8	1521	0.5%		
Ruminjo and Ngugi, 1993 [5]	30	1999	1.5%		
Cisse et al., 1997 [4]	7	800	0.9%		
Kidan et al., 2001 [9]	0	148	0.0%		
Gordon-Maclean et al., 2014 [18]	11	518	2.1%		
			AE rate (weighted average)	Lower limit	Upper limit
Total	681	17,705	3.85%	3.15%	4.54%
Total excluding Jack and Chao, 1992 [8]	199	12,523	1.59%	0.90%	2.28%

*AE* Adverse event

These data suggest that an absolute rate of approximately 3% would be expected and that we would expect no greater than 5%, based on the upper limit of the 95% CI. In addition, in the clinical judgment of EngenderHealth staff and outside experts, we have determined that a noninferiority margin of 2% is appropriate because it implies that up to a 5% AE rate would be clinically acceptable. In other words, if the upper limit of the two-sided 95% CI for the difference in AE rates (CO minus AMO) lies fully to the left of the 2% noninferiority margin, we will have proved noninferiority of tubal ligation by minilaparotomy conducted by COs at a level of significance of α = 0.05.

Assuming a 3% major AE rate in the control group (AMOs), we will demonstrate noninferiority within the margin of 2% at a one-sided significance level of α = 0.05 and a power of 80% (calculated when AE rates in both arms are the same) with a sample size of 895 per arm (1790 women in total). Adjusting by 10% for loss to follow-up, protocol violations, and withdrawals, this would result in a total sample size of 1969 women, rounded to 1970.

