### Statistical methods

We will develop a detailed analysis plan that covers both the final analysis and the planned interim analysis prior to initiation of the analysis. The primary outcome of the trial is major AEs within 42 days of the tubal ligation by minilaparotomy (i.e., the proportion of participants experiencing a major AE by day 42 postsurgery) in an intention-to-treat (ITT) analysis. We will conduct the primary analysis for the ITT population. The ITT population would include participants for whom the protocol is violated (i.e., participants who are randomized to have their procedure done by a CO but in fact have the procedure done by an AMO, or participants who are randomized to have their procedure done by an AMO but in fact have the procedure done by a CO) and withdrawals/discontinuations. We will also conduct a per-protocol analysis for the primary outcome if we have participants who do not receive the treatment to which they were randomly allocated.

Unlike a superiority trial, where the treatment effect is the primary parameter of interest, the interpretation of a noninferiority trial’s results depends on the location of the CI for the effect of the experimental treatment relative to the margin of noninferiority and a null effect [22]. The primary analysis will be interpreted as follows. If the whole 95% CI lies above the noninferiority margin of 2%, the experimental intervention will be declared “inferior.” If the whole 95% CI lies below the noninferiority margin, the intervention will be considered to be “noninferior” to the standard treatment. If the 95% CI includes the noninferiority margin, study results will be deemed inconclusive. Finally, if the entire 95% CI lies completely below zero, the new treatment may be considered superior to the standard treatment.

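### The sample size assumes a one-sided 5% test, but noninferiority is judged on a two-sided 95% CI, so the stated 80% power is about 70%

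*Protocol article*

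**What the plan says.** All statements are in the Protocol article.

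- **Design level.** The last paragraph of *Rationale for the noninferiority hypothesis and sample size calculation* says "we will demonstrate noninferiority within the margin of 2% at a one-sided significance level of". The level it gives is 0.05, and the power is 80%. Power is computed with equal event rates in the two arms and a control rate of 3% ("Assuming a 3% major AE rate in the control group (AMOs"). The result is 895 per arm, 1790 in total, raised by 10% to 1969 and rounded to 1970.
- **Decision rule, first statement.** The paragraph before it declares noninferiority "if the upper limit of the two-sided 95% CI for the difference in AE rates (CO minus AMO) lies fully to the left", where the reference point is the 2% margin. It describes this as proof "at a level of significance of α = 0.05", without saying whether that level is one-sided or two-sided.
- **Decision rule, second statement.** *Statistical methods* repeats the criterion for the primary analysis: "If the whole 95% CI lies below the noninferiority margin", the CO arm is called noninferior. If the interval includes the margin, the result is inconclusive.

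The article nowhere mentions a 90% CI or a one-sided 95% limit.

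**The concern.** Requiring the upper limit of a two-sided 95% CI to be below the margin is the same as a one-sided test at 0.025 (critical value 1.96). The sample size uses one-sided 0.05 (critical value 1.645). These are different tests of the same hypothesis, and nothing in the article reconciles them.

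Two things are at stake. First, the stated power does not belong to the rule that will be applied, so an inconclusive result is more likely than readers are told, even if COs and AMOs are equally safe. Second, two levels are on record for the primary claim. If the 95% upper limit fell above 2 points and the 90% limit below it, the sample size sentence could be cited for success and the decision rule for an inconclusive result. The trial is unmasked and is meant to inform government regulation, so that opening should be closed before the analysis.

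**Working it through.** **Inputs from the article:** event rate p = 0.03 in both arms; margin 0.02; 1:1 allocation; 895 evaluable per arm; 1970 randomised, which is 985 per arm; power 80%, so z_b = 0.842.

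**Formulas** (unpooled normal approximation):

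- n per arm = (z_a + z_b)² × 2p(1 − p) / margin²
- power = Φ(margin / √(2p(1 − p)/n) − z_a)

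Here 2p(1 − p) = 2 × 0.03 × 0.97 = 0.0582, and 0.0582 / 0.02² = 145.5.

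**Step 1: reproduce the plan's figure.** At one-sided 0.05, z_a = 1.645 and n = (1.645 + 0.842)² × 145.5 = 899.6 (unrounded z values), so 900 per arm. The article's 895 is 0.6% lower. At 895, the standard error is √(0.0582/895) = 0.008064, the ratio 0.02/0.008064 is 2.480, and power = Φ(2.480 − 1.645) = 79.8%. The stated 895 is therefore a one-sided 5% calculation.

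**Step 2: power under the stated decision rule.** With z_a = 1.960, power at 895 = Φ(2.480 − 1.960) = Φ(0.520) = 69.9%.

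**Step 3: no attrition.** At 985 per arm, the standard error is √(0.0582/985) = 0.007687, the ratio is 2.602, and power = Φ(2.602 − 1.960) = 74.0%. The one-sided 0.05 test would give 83.1%.

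**Step 4: size needed for 80% power under the CI rule.** n = (1.960 + 0.842)² × 145.5 = 1142.01 (unrounded z values), so 1143 per arm before attrition.

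**Step 5: check without the normal approximation to power.** Exact binomial enumeration at 3% in both arms, under the 95% CI rule:

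| Evaluable per arm | Normal approximation | Exact, Wald limits | Exact, score limits |
|---|---|---|---|
| 895 | 69.9% | 69.9% | 67.6% |
| 985 | 74.0% | 74.3% | 72.2% |

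**Step 6: sensitivity to the event rate** (895 per arm, 95% CI rule, normal approximation):

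| Rate in both arms | Source | Power |
|---|---|---|
| 1.59% | Table 3 without the outlier | 92% |
| 3% | Planning assumption | 69.9% |
| 3.85% | Table 3, all studies | 59% |

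The rate at which 895 per arm gives 80% power solves p(1 − p) = 895 × 0.02² / (2 × 7.849) = 0.0228, where 7.849 = (1.960 + 0.842)² with unrounded z values. This gives p of about 2.33%.

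**The case against.** The strongest counter-case has five parts.

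- **The mismatch is conservative.** The rule to be applied is stricter than the design level, so a false claim of noninferiority becomes less likely. This stands: the error is confined to power.
- **About 70% is conditional.** It needs a 3% rate and exactly 895 evaluable per arm. Protocol violators stay in the ITT analysis and only women with missing data drop out, so planned power lies between about 70% and 74%. If the true rate were near 1.59%, power would be ample. This also stands, but 3% is the rate the protocol chose, and its stated power has to hold there. Neither 895 nor 985 per arm reaches 80%.
- **The significance label on the CI rule is not wrong in itself.** A two-sided 95% CI corresponds to a two-sided level of 0.05. That reading is fair. The label is ambiguous, and the contradiction comes from the words one-sided in the sample size sentence.
- **The 95% CI is already fixed twice.** The room for choosing a 90% interval is therefore narrow. It comes only from the sample size sentence, but it exists while that sentence stands.
- **Enrolment and follow-up are complete** according to *Trial status*, so power cannot be restored. That limits the remedy to wording and does not make the stated power correct.

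**Conclusion.** The concern holds. The power statement is wrong as written: 80% belongs to a one-sided 5% test that the protocol does not use for its conclusion. Under the two-sided 95% CI rule, with 3% in both arms and a 2-point margin, power is about 70% at 895 evaluable per arm and about 74% at 985.

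At 895 per arm, the probability of not showing noninferiority when the two provider groups are equally safe is 30.1% instead of the 20.2% implied by the design calculation, a ratio of about 1.5. These figures rest on the 3% planning rate and would be better at a lower rate and worse at a higher one. Type I error is unaffected.

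**What to change.** Use one error rate throughout.

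1. Keep the two-sided 95% CI rule and state its one-sided level as 0.025, in place of the significance label that gives no sidedness.
2. In the sample size paragraph, delete the one-sided 0.05 wording. Restate power as about 70% for 895 evaluable per arm, and about 74% if all 985 are evaluable, both at a 3% rate.
3. Record in the analysis plan, which the article says will be written before the analysis begins, that no 90% CI will be used to claim noninferiority.

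A one-sided 5% test with a two-sided 90% CI would also be internally consistent. The 95% rule is preferable because the article states it twice and it is the stricter one. Relaxing the criterion after follow-up has ended in an unmasked trial would be hard to defend.

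The cost is wording only, and the stated power becomes less favourable. No additional women are needed. The 1143 per arm that would restore 80% power is no longer an option because enrolment is closed.

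### The 10% attrition allowance multiplies 1790 by 1.10 instead of dividing by 0.90, so 1970 women cover about 9.1% loss, not 10%; the effect on power is about 0.3 points.

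*Protocol article*

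**What the plan says.** All the figures are in the protocol article, section Rationale for the noninferiority hypothesis and sample size calculation. The inputs are a 3% control rate ("Assuming a 3% major AE rate in the control group (AMOs"), a 2-point margin ("we have determined that a noninferiority margin of 2% is appropriate"), testing "at a one-sided significance level of α = 0.05", and "a power of 80% (calculated when AE rates in both arms are the same"). Allocation is equal: "Randomization is in a 1:1 ratio" (section Generation of allocation sequence and random allocation). These lead to noninferiority being shown "with a sample size of 895 per arm (1790 women in total").

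The next sentence moves from evaluable to enrolled women: "Adjusting by 10% for loss to follow-up, protocol violations, and withdrawals, this would result in a total sample size of 1969 women", rounded to 1970. No inflation formula is shown.

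Two parts of the Statistical methods section bear on what the 10% means. The primary analysis is by intention to treat, and that population keeps women treated by the other cadre as well as withdrawals; a per-protocol analysis of the primary outcome is added if any woman does not receive her allocated treatment. Missing observations are neither analysed nor imputed, and data from women who withdraw count up to the time they leave.

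**The concern.** An allowance for attrition is normally a fraction of the women enrolled. To have N left after losing a fraction L, one enrols N / (1 − L). Multiplying by (1 + L) always gives too few, because the loss is then taken from a larger base than the one used for the mark-up. The stated total matches the multiplication exactly.

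Missing outcomes are not imputed, so each woman without outcome data comes straight off the evaluable number. If 10% is the expected loss, the enrolled total does not deliver the 1790 that the same section ties to 80% power, and the power statement is slightly too favourable. What is at stake is the accuracy of a published sample size statement, not the viability of the trial.

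**Working it through.** **Inputs** (from the sample size section): event rate 0.03 in both arms, margin 0.02, one-sided α = 0.05, power 80%, 895 per arm or 1790 in total, allowance 10%, enrolled total 1969 rounded to 1970.

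**1. The base number.** Unpooled normal approximation, per arm:

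n = (z_α + z_β)² × 2 × 0.03 × 0.97 / 0.02² = (z_α + z_β)² × 0.0582 / 0.0004

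- Quantiles rounded to 1.64 and 0.84: 2.48² × 145.5 = 894.9, so 895.
- Unrounded quantiles: 899.6, so 900.

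The stated 895 is reproduced to within about 0.5%. I take 895 and 1790 as given from here on.

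**2. The stated total.** 1790 × 1.10 = 1969. This reproduces the plan's figure exactly.

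**3. The total needed if 10% of enrolled women are lost.** 1790 / 0.90 = 1988.9, so 1989 (1990 for equal arms). That is 19 to 20 more than 1970, a difference of about 1%.

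**4. What 1970 delivers.**

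- At 10% loss: 1970 × 0.90 = 1773 evaluable, or 886.5 per arm.
- Shortfall: 1790 − 1773 = 17 women, and 17 / 1790 = 0.95%.
- Largest loss that still leaves 1790: 1 − 1790 / 1970 = 180 / 1970 = 9.14%.

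**5. Effect on power** at one-sided 0.05 and a true difference of zero:

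power = Φ(0.02 / √(0.0582 / n) − 1.645)

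| Evaluable per arm | 0.02 / SE | Power |
|---|---|---|
| 895 | 2.480 | 79.8% |
| 886.5 | 2.468 | 79.5% |

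The loss is about 0.3 percentage points.

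**6. When the shortfall arises.** Ten percent of 1970 is 197 women, and 1970 can lose 180 before falling below 1790. So if at least 17 of those 197 stay in the analysis with outcome data, for example as protocol violators kept under intention to treat, 1790 is reached and there is no shortfall in the primary analysis.

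**The case against.** The strongest reply is that the protocol says only that it adjusts by 10%. It does not say that 10% of enrolled women are expected to be lost, or that 1790 must remain after such a loss. Read literally, it adds a 10% margin and does so correctly. This reading is possible. But the sentence names what the margin is for, namely loss to follow-up, violations and withdrawals, and these are naturally counted as a share of those enrolled. Under either reading it is accurate, and more useful, to say that 1970 covers about 9.1% loss.

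A second reply is that not all of the 10% leaves the primary analysis. This stands. Intention to treat keeps violators and withdrawals, so 1773 is the evaluable number only if the whole 10% lacks outcome data, or for the per-protocol set. A reader might infer that the primary analysis will certainly be 17 women short; the protocol does not support that.

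A third reply is that the effect is negligible and enrolment is over (Trial status gives completion on 16 June 2017). Both are true, and they limit the remedy to a correction of the text.

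Three stronger readings are also tempting and should be set aside:

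- **The base should be 900 per arm, hence 2000 enrolled.** The 0.5% gap fits quantiles rounded to two decimals, and the protocol does not print its formula. That is not a documented error.
- **Protocol violations should come out of the allowance.** Because a per-protocol analysis of the primary outcome is also foreseen, allowing for them protects that set. Removing them would be a preference.
- **Power is really about 69%.** That figure comes from judging noninferiority "if the upper limit of the two-sided 95% CI for the difference in AE rates (CO minus AMO) lies fully to the left" of the margin, which is a one-sided 0.025 rule, while the sample size uses one-sided 0.05. That mismatch is a separate issue. Under the interval rule, power is about 69.9% at 895 per arm and 69.4% at 886.5, so attrition again accounts for only about 0.4 points.

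**Conclusion.** The point holds as a minor arithmetic slip. As an allowance for 10% loss, the stated 1969 uses the wrong operation; the corresponding total is 1989, and 1970 covers about 9.1%. The consequence is at most 17 evaluable women and about 0.3 points of power (79.8% to 79.5%) at the stated one-sided 0.05.

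This rests on three assumptions: that 10% is the expected loss among enrolled women; that all of it lacks outcome data, or that the per-protocol set is meant; and that the unpooled normal approximation with a 3% rate in both arms is adequate for the power figures. If the loss from the primary analysis is 9.1% or less, the planned 1790 is met and only the wording needs correcting. No conclusion of the trial depends on this point.

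**What to change.** Replace the inflation sentence in the sample size section with one that says what 1970 delivers: enrolling 1970 women leaves 1790 evaluable if about 9.1% are lost; if 10% are lost, about 1773 are evaluable, with power of about 79.5% at the stated one-sided 0.05 (unpooled normal approximation). It would help to add that the 10% case assumes all of those women lack outcome data, or refers to the per-protocol set.

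No added enrolment is needed, and neither the 895 per arm nor the content of the allowance has to change for this point. The cost is one sentence and a power figure slightly below the 80% now printed.
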